#### Measures and variables

A general assessment, together with demographics, will include measures of psychiatric symptoms (in particular negative symptoms), psychosocial functioning and time perception. Variables related to daily time use will include the number of daily hours spent in different activities: paid work, study, travel, doing nothing/resting, social/leisure activities, activities related to child/household care, voluntary activities, sport, and hobbies. Table 2 shows a comprehensive overview of the measures and areas of investigation; all reported instruments have been tested for validity and reliability in Italian: Table 2 shows the reference of the original paper for each instrument, and the reference of the Italian validation study. Time use assessments will consist of a pre-filled daily diary (to be completed twice a week, on a working day and on a weekend day) adapted from the ISTAT’s national survey on time use, asking participants to retrospectively report the daily time spent in different activities. The time spent in each activity will be calculated as number of hours per week.

**Table 2 Tab2:** Assessment measures, domains and subjects receiving the assessment

Instrument/Reference (original and Italian validation)	Domain	Study group			
		Residential patients	Outpatients	Healthy controls	Staff
Mini Mental State Examination (MMSE) (Cockrell & Folstein, 2002 [53]; Measso et al., 1993 [54])	Cognitive functioning	X	X	X	
Brief Psychiatric Rating Scale (BPRS) (Overall and Gorham, 1962 [55]; Morosini et al., 1995 [56])	Psychiatric functioning	X	X		
Brief Negative Symptom Scale (BNSS) (Strauss et al. 2012 [57]; Mucci et al., 2015 [58])	Negative symptoms	X	X		
Specific Levels of Functioning Scale (SLOF) (Schneider et al., 1983 [59]; Mucci et al. 2014 [60])	Current functioning and behaviour	X	X		
World Health Organization Quality of Life Brief version (WHOQOL-Bref) (Whoqol Group, 1998 [61]; de Girolamo et al., 2000 [62])	Quality of life	X	X		
World Health Organization Disability Assessment Schedule 2.0 (WHODAS 2.0) (Gold, 2014 [63]; Federici et al., 2009 [64])	Psychosocial functioning	X	X		
Zimbardo Time Perspective (ZTPI-short form) (Zimbardo & Boyd, 2015 [65]; Laghi et al., 2009 [66])	Attitude towards time	X	X	X	
Positivity Scale (P Scale) (Caprara et al., 2012 [67])	Positivity assessment	X	X		
Time Use Survey (TUS) (see HETUS, 2019 [68])	Use of daily time	X	X	X	
Verona Service Satisfaction Scale (VSSS) (Ruggeri et al., 1993 [69])	Satisfaction with services	X			
Working Alliance Inventory Short Patient and Therapist versions (WAI-PT and WAI-TP) (Hatcher & Gillaspy, 2006 [70]; Lo Coco et al., 2011 [71])	Patients’ and staff relationships	X			X
Camberwell Assessment of Need Patient and Staff versions (CAN) (Phelan, 1995 [72]; Ruggeri et al., 1999 [73])	Health and social needs	X			X
Ward Atmosphere Scale (WAS) (Moos & Houts, 1968 [74]; Burti et al., 1990 [75])	Individual perception of the ward atmosphere	X			X
General Health Questionnaire (GHQ-12) (Goldberg, 1970 [76]; Fontanesi et al., 1985 [77])	General health evaluation				X
Maslach Burnout Inventory (MBI) (Maslach, 1981 [78]; Sirigatti et al., 1988 [79])	Level of Burnout				X
Quality Indicator for Rehabilitative Care (QuIRC-SA) (Killaspy, 2016 [80])	Quality of the rehabilitative service				X (RF’s manager)
Smartphone app	Use of daily time	X	X	X	
Smartphone app	Perceived energy	X	X	X	
Smartphone app	Mood	X	X	X	
Actigraphy	Physical activity	X	X	X	

#### Procedure

Clinicians and mental health workers at the participating sites will receive a training session on questionnaires’ administration. Participants will be asked to complete the instruments and will receive a 20-min training session on daily diary instructions. A web portal that will allow clinicians to directly fill in the study questionnaires will be developed, and this procedure will be guided with clear and simple user interfaces. The software will perform data validation to highlight possible errors. If there is no local access to an internet connection, it will be possible to use an off-line desktop application with the same functionalities but with the ability to locally save the collected data on a computer. Data will then be uploaded to the online database when the internet connection is available.

### Study 2 design

#### Participants

The sample will include 300 patients living in RFs (G1) and RF staff (approximately 1 staff member every 5 patients).

#### Measures and variables

Patients will be evaluated using a set of standardized instruments, as summarized in Table 2. The variables being studied will encompass quality of care and quality of relationships between patients and staff, level of well-being and level of burnout of RF staff, and quality of the facility assessed with the QuIRC-SA (i.e., living environment, treatments and interventions, therapeutic environment, self-management and autonomy, social interface, human rights, recovery-based practice).

#### Procedure

RF staff and RF managers will receive a specific training session about questionnaire administration. The facility manager will fill in the QuIRC-SA.

### Study 3 design

#### Participants

The sample will include a sub-group of at least 50 RF patients (drawn from G1), 50 outpatients (drawn from G2) and 50 healthy controls from the general population matched by age and gender. This latter group will also complete the TUS. Healthy controls will be recruited through ads, both using the project’s website and spreading the news of the study through social networks.

#### Measures and variables

We will perform a time use evaluation with the ESM data, and these reports will be compared with retrospective paper-and-pencil assessments to evaluate the degree of consistency between the two information sources. Patients and healthy controls performing the ESM assessment will also be asked to wear a multi-sensor device (actigraphy) to assess levels of PA over the course of 1 week. For the ESM assessment, participants will be equipped with smartphones where a DiAPAson app will be installed. The answer to the smartphone’s prompt will allow easy evaluation of the following:
the specific activity being carried out by the patient (e.g., paid work, leisure, resting/doing nothing);mood (i.e., rating of different adjectives on a scale from 0 to 100; e.g., “sad”, “happy”, etc.);perceived level of energy (i.e., rating of different adjectives on a scale from 0 to 100; e.g., “active”, “tired”, etc.).

#### Procedure

Each participant will receive a 30-min training session on the ESM procedure. Participants will install the DiAPAson app on their smartphones (or will be lent a smartphone if they do not have one) and will be asked to carry the device with them over a 7-day period. The smartphone will generate a prompting auditory “recall” signal, sending a notification 9 times a day at random intervals between 7 AM and 11 PM. Participants will have to complete the ESM questionnaire on the smartphone screen (it takes approximately 1 min and has to be completed no later than 30 min after being prompted). ESM reports will allow the assessment of some of the variables examined in the TUS, as well as perceived energy and mood.

After a short training on PA assessment, participants will be asked to wear a multi-sensor device, ActiGraph GT9X Link (manufactured by ActiGraph, Pensacola, FL 3250, USA), continuously over 7 consecutive 24-h periods. The device will be worn on the non-dominant arm and set to record 60-s epochs, computing a total activity count for each active minute of the day. This method relies on a wearable device (combining accelerometer with measurements of heat production and skin conductivity) that measures physiological variables and bodily movements over prolonged periods of time. An algorithm converts raw data into estimates of Energy Expenditure (EE), which are expressed both in kcal/min and Metabolic EquivalenTs (METs) [81]. The multi-sensor device has been shown to provide accurate results for estimating EE and time spent in various activities and to provide valid estimates of EE in the general population [82]. The following PA parameters will be measured: (i) average physical activity: the average of all active minutes during days and nights; (ii) total idle time as well as sleeping (including sleep latency, sleep efficiency and total sleep time): average number of inactive minutes between morning alarm and time when going to bed; (iii) energy expenditure; (iv) MET rates; and (v) body position. These data will be collected as integrated activities every 60 s using arbitrary units.

Measurements via smartphone and actigraphy will be simultaneous (i.e., during the same week). Outpatients and healthy controls participating in the ESM and PA monitoring will receive a € 25 reimbursement in supermarket vouchers as compensation for travel expenses to receive the training. All these data will be saved in a secure database for future analysis. At the end of the assessment week, the project web portal will be used to upload the armband data.

### Recruitment and data collection

Eligible participants will be recruited from a large number of RFs across the entire country, allowing meaningful comparisons of facilities and services located in different areas. Consent forms will be collected according to the local ethical committee requirements. Participants will be matched by age, gender and diagnosis. Both residential patients and outpatients will be recruited by treating clinicians; outpatients meeting inclusion criteria will be consecutively invited to join the study. Similar number of participants will be recruited at each participating centre, also accounting for the specific characteristics of each participating facility. Overall, patients to be recruited in each center will range from 15 (smaller ones) to 40 subjects (bigger ones).

As spelled out in the original protocol approved by the funding agency, data collection will last 8 months. Questionnaires will be administered as participants are enrolled. Patients and controls participating in Study 3 (and Objective 3) will be invited to start the ESM and the monitoring of PA immediately after questionnaire administration. The administration of tools to be filled by clinicians for all patients (BPRS, BNSS and SLOF) will last approximately 1 hour; the administration of tools to be filled by clinicians only for residential patients (e.g., WAI-TP, CAN and WAS) will last approximately one additional hour. Self-administered tools (e.g., WHOQOL-Bref, WHODAS 2.0, ZTPI, P Scale, CAN, VSSS, WAI-PT, WAS) for patients will take approximately 15 min each, and can also be filled at different times. Training for both TUS, ESM and actigraphy administration will last approximately 40 min and will be organized in small groups of 2–3 participants.

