## Methods/Design

### Study design and management

Data collection will take place in many Departments of Mental Health (DMHs) and RFs across the country, and will start in June 2020; data collection will end on May 2021. The project will be coordinated by the IRCCS Fatebenefratelli of Brescia (coordinating centre), the DMH of Modena and the DMH of Pavia. To date, approximately over 35 DMHs and RFs have expressed written interest for inclusion in the project (see Acknowledgements for a list of participating facilities). Formal agreements are currently being finalized.

Participants will be selected according to the inclusion and exclusion criteria shown in Table 1. They will approve and sign an informed consent form before inclusion in the study. The flow diagram shown in Fig. 1 provides a clear picture of enrolment and assessment procedures of all study subjects.

**Table 1 Tab1:** Patients’ recruitment: inclusion and exclusion criteria

	Inclusion criteria	Exclusion criteria
All groups	- Age 20–55 years old; - Good knowledge of Italian language.	- Inability to provide informed consent (because of low education, or cognitive impairment); - Severe cognitive deficit (MMSE equal or lower than 24.0); - Lifetime diagnosis of substance use disorder according to DSM-5 criteria (APA, 2013 [52]); - History of clinically significant head injury; - Cerebrovascular, neurological disease.
G1 and G2	- SSD diagnosis according to DSM-5 (APA, 2013 [52]); - In charge to a RF or to a DMH as outpatient.

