### Study 1 design

#### Participants

The sample will include 300 residential patients diagnosed with SSD (G1), matched by age and gender to 300 outpatients (G2). General population data will be extracted from the National Institute of Statistics (ISTAT) survey “*Uso del tempo quotidiano*”, a national survey that assesses how people spend their time, which was conducted in 2013 in Italy (ISTAT, https://www4.istat.it/it/prodotti/microdati#file_ricerca) in a representative sample of the Italian population including approximately 27,000 families (with a total of approximately 60,000 surveyed individuals) living in 508 municipalities (out of over 8000 Italian municipalities) of different sizes.

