### Data analyses

#### Study 1

Data on daily time use in the different groups will be compared using parametric and non-parametric methods depending on the distribution of the investigated variables. Correlation estimates (Pearson or Spearman) will be used to assess the associations between the severity of psychiatric symptoms and the amount of sedentary time.

Sample size was calculated based on Cella and colleagues’ study [12], which compared patients with SSD (*N* = 170) and a general population sample (*N* = 1124). Their results showed that the average time spent “doing nothing” (target) in the patient group was 5.17 h per day, while for the general population, it was 0.76 h with a standard deviation of 5 for both groups. With such data, the effect size for a linear model is 0.44. As a precaution, assuming a lower effect size equal to approximately 0.15, using ANCOVA (including age and gender in the model) with three groups, and choosing a power of 0.8, the estimated total sample size is equal to *N* = 435. Moreover, considering a total of approximately 25 different recruitment centres, the correction for the design effect (DE = 1 + (435/25–1)*0.02 = 1.3, with an intraclass correlation coefficient equal to 0.02) leads to a sample size of about *N* = 570, which was increased to *N* = 600 (300 for each group) to account for possible dropouts of about 10%. Finally, 300 matched subjects randomly sampled from the ISTAT general population sample will be added as third group, for a total of *N* = 900 subjects evaluated for daily time use.

#### Study 2

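### Residents and outpatients are matched on personal factors but not on area, so a regional difference can enter the contrast that is read as an effect of setting

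*Protocol article*

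**What the plan says.** The protocol article gives the matching rule twice. Under Study 1 design, Participants, the 300 residents are "matched by age and gender to 300 outpatients (G2"). Under Recruitment and data collection the rule is wider: "Participants will be matched by age, gender and diagnosis". Area and centre appear in neither list.

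On where patients come from, Table 1 requires that a patient be "In charge to a RF or to a DMH as outpatient". Recruitment and data collection describes patients as "recruited from a large number of RFs across the entire country, allowing meaningful comparisons of facilities and services located in different areas". It adds "Similar number of participants will be recruited at each participating centre", with 15 to 40 patients per centre, but fixes no ratio of residents to outpatients within a centre or area. Study design and management describes sites that have declared interest, and Limitations says that facilities are not a random selection and that suitable corrections will be made at analysis.

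For the general population, the ISTAT survey covers people "living in 508 municipalities (out of over 8000 Italian municipalities) of different sizes". Data analyses, Study 1, says "300 matched subjects randomly sampled from the ISTAT general population sample will be added as third group" and does not list the matching variables there. The same section derives the sample size "using ANCOVA (including age and gender in the model) with three groups". Strengths says that the project will assess the effect of the everyday setting, RF against community.

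**The concern.** The plan counts geographic spread among its advantages, yet nothing it states keeps that spread equal between residents and outpatients. Work, travel, household and leisure time may vary with region and town size. If one area supplies mainly residents and another mainly outpatients, part of the area difference is reported as an effect of living in an RF.

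The correction for centres does not help. The design effect enlarges the sample to restore precision; it does not move a biased contrast back to its true value.

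The resident-outpatient contrast is the exposed one. The Background section on previous Italian studies says it is unknown whether outpatients spend more, the same or less time in meaningful activities than residents. With even the sign open, a modest bias could affect the conclusion.

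**Working it through.** **1. The plan's own figures.** Inputs from Data analyses, Study 1: means 5.17 and 0.76 h/day, SD 5, f = 0.15, power 0.8, three groups, 25 centres, ICC 0.02.
- Effect size: (5.17 − 0.76)/5 = 0.882; half of this is 0.441, matching the stated 0.44.
- Sample size: a noncentral F calculation with alpha 0.05 (assumed; not stated) gives N = 432, against the stated 435.
- Design effect: 1 + (435/25 − 1) × 0.02 = 1.328; 435 × 1.328 = 578, and with the rounded 1.3, 566. The stated figure is about 570.

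These figures reproduce, and the point does not depend on any of them being wrong.

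**2. Between-centre variation that the plan allows.** Total variance is 5² = 25 h². Between-centre variance is 0.02 × 25 = 0.5 h², an SD of √0.5 = 0.71 h/day. Centres lie within areas, so a difference between areas is part of this 0.5 h².

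**3. Bias formula.** With two areas, bias = (difference between groups in the share from one area) × (difference between areas in h/day). The document gives neither factor; the values below are assumptions.

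**4. Mild case.** Shares 60% and 40%, areas 1 h/day apart: 0.20 × 1 = 0.2 h/day. Area would then account for 0.24 × 1² = 0.24 h², about half of the 0.5 h² available.

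**5. Ceiling for shares of 70% and 30%.** Let area explain all between-centre variance.
- Two areas of equal size overall: 0.25 × gap² = 0.5, gap = 1.41 h/day, bias = 0.40 × 1.41 = 0.57 h/day.
- Using the 70/30 split within a group: 0.21 × gap² = 0.5, gap = 1.54 h/day, bias = 0.40 × 1.54 = 0.62 h/day.

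The ceiling is therefore about 0.6 h/day for shares this uneven. More extreme separation would raise it.

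**6. Effect on the test.** For 300 against 300, the standard error is 5 × √(2/300) = 0.408 h/day. If setting has no effect, a nominal two-sided 5% test has these false-positive rates:

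| Bias (h/day) | Bias / SE | Rejects |
|---|---|---|
| 0.2 | 0.49 | 7.8% |
| 0.57 | 1.39 | about 28% |

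**7. Scale.** The resident-outpatient difference detectable with 80% power is (1.96 + 0.84) × 0.408 = about 1.1 h/day, or about 1.3 h/day with the design effect. For patients against the population, the gap that the plan cites is 5.17 − 0.76 = 4.41 h/day.

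**The case against.** The strongest reply is that nothing in the document shows the area mix to be unequal. Table 1 is an eligibility criterion and does not say that an area supplies only one group. Treating clinicians recruit both groups, and some areas may supply both. No centre can exceed 40 of 600 patients, about 7%. This stands: the document leaves imbalance possible and does not establish it.

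Several stronger readings are tempting and are not supported:
- **That the bias could be 0.8 h/day** (70/30 shares, areas 2 h/day apart). Area alone would contribute 0.21 × 4 = 0.84 h², an ICC of 0.84/25 = 0.034, above the plan's 0.02.
- **That the ISTAT group is known not to be matched on area.** It is called matched without a list of variables, so one can say only that no area variable is named.
- **That area is excluded from the analysis model.** Age and gender are named in the sample-size derivation; the sentence on the analysis fixes no covariates.
- **That the comparison with the population is in doubt.** A bias of 0.6 h/day would not overturn a gap of 4.41 h/day in time spent doing nothing.

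It can also be said that Limitations promises corrections, and that their detail belongs in a full protocol or analysis plan that is not shown. That is fair as to detail. However, the promise follows a remark on whether the facilities represent Italian services. It does not secure balance between groups, and no later correction can separate area from setting where an area has supplied only one group. The matching rule is stated in full, twice, and area is not in it.

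**Conclusion.** The concern holds for the resident-outpatient contrast, as a risk left open by the stated matching rule and not as a demonstrated bias. Its size cannot be computed from the document. Under assumed shares, and taking the plan's SD of 5 and ICC of 0.02 as true, it runs from 0.2 h/day in a mild case to about 0.6 h/day at 70/30 against 30/70, or up to about half of the detectable 1.1 h/day. These limits depend on the ICC, which is itself a planning assumption. No stated figure is wrong. For the general-population comparison the point is secondary. It deserves a change because the plan presents the RF-community difference as an effect of setting and the remedy is cheap.

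**What to change.** - **Matching** (Study 1 design, Participants; Recruitment and data collection): add geographic area to the list, and frequency-balance outpatients to residents within area where participating sites allow. Strict pairing within a centre is not needed.
- **Analysis** (Data analyses, Study 1): include area as a covariate in the group comparison.
- **ISTAT group**: list the matching variables and, if the microdata carry area codes, draw the 300 comparators by age, gender and area. The document does not say whether such codes exist.

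The cost is wording in three sections, some constraint on how site quotas are filled, and a few degrees of freedom in the model. The balancing has to be set before recruitment, which the Study status section places after the date of this version.

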### Data analyses

#### Study 1

Data on daily time use in the different groups will be compared using parametric and non-parametric methods depending on the distribution of the investigated variables. Correlation estimates (Pearson or Spearman) will be used to assess the associations between the severity of psychiatric symptoms and the amount of sedentary time.

Sample size was calculated based on Cella and colleagues’ study [12], which compared patients with SSD (*N* = 170) and a general population sample (*N* = 1124). Their results showed that the average time spent “doing nothing” (target) in the patient group was 5.17 h per day, while for the general population, it was 0.76 h with a standard deviation of 5 for both groups. With such data, the effect size for a linear model is 0.44. As a precaution, assuming a lower effect size equal to approximately 0.15, using ANCOVA (including age and gender in the model) with three groups, and choosing a power of 0.8, the estimated total sample size is equal to *N* = 435. Moreover, considering a total of approximately 25 different recruitment centres, the correction for the design effect (DE = 1 + (435/25–1)*0.02 = 1.3, with an intraclass correlation coefficient equal to 0.02) leads to a sample size of about *N* = 570, which was increased to *N* = 600 (300 for each group) to account for possible dropouts of about 10%. Finally, 300 matched subjects randomly sampled from the ISTAT general population sample will be added as third group, for a total of *N* = 900 subjects evaluated for daily time use.

#### Study 2

To evaluate how the level of burnout of the staff affects the quality of the therapeutic relationships with the staff, correlation estimates (Pearson or Spearman) will be used. The influence of the burnout level (categorized as high/low) of staff (each staff member associated with a patient) on the quality of the therapeutic relationship with patients (WAI-pt) will be investigated by comparing groups (patients and staff in RFs) with generalized linear or linear models. To evaluate the associations between the quality of RFs rated by service managers and patient experiences of care, in accordance with Killaspy and colleagues [83], we will perform multilevel modelling analyses of associations between service user ratings (level 1 data) as dependent variables with unit QuIRC-SA domain ratings (level 2 data) as independent variables. The models will also include potential mediators (i.e., age, gender, and level of severity of psychiatric symptoms as assessed in Study 1).

#### Study 3

Appropriate tests will be used to compare the daily time use with routine methods and with ESM according to the distribution of the data. In particular, frequencies and corresponding chi-square tests, as well as Cohen’s kappa concordance index, will be used to compare ESM reports and retrospective assessments and to assess the degrees of consistency between the two sources of information.

The sub-sample chosen for Study 3 (*N* = 150, including 50 randomly chosen from Group 1, 50 randomly chosen from Group 2 and 50 healthy subjects) is in line with the sample size of Merikangas and colleagues [84]. Multilevel models (MLM [85]) will be used to simultaneously evaluate within- and between-subject associations, taking into account repeated measurements. In addition, cross-lagged analyses will be carried out to examine the directionality of the measured effects. Comparisons of PA quantity variables between groups will be evaluated using linear and generalized linear models.

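### The Study 1 sample-size paragraph does not add up (dropout margin, cluster size, and a three-group total given to two patient groups), although no shortfall in power is shown

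*Protocol article*

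**What the plan says.** All the figures below are in the Study 1 part of Data analyses in the Protocol article, unless another section is named.

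- The source means for time doing nothing are 5.17 h per day in patients; in the general population "it was 0.76 h with a standard deviation of 5 for both groups". These give an effect size of 0.44.
- The plan then takes a cautious value, "assuming a lower effect size equal to approximately 0.15". For an analysis of covariance on three groups, adjusted for age and gender and with target power 0.8, it arrives at a total of 435.
- Clustering is allowed for with about 25 centres and an intraclass correlation of 0.02: "DE = 1 + (435/25–1)*0.02 = 1.3". This gives about 570.
- 570 becomes 600: "300 for each group) to account for possible dropouts of about 10" per cent.
- Another 300 matched ISTAT subjects form the third group, for 900 in all.

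Recruitment and data collection adds that "patients to be recruited in each center will range from 15 (smaller ones) to 40 subjects (bigger ones"). Study design and management reports that more than 35 departments and facilities had expressed interest, with agreements not yet final.

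**The concern.** Three steps of the chain do not fit together.

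1. Going from 570 to 600 is too small an increase for a 10% loss.
2. The cluster size in the design effect is not the number of patients a centre will recruit. It divides a total that includes general-population subjects by the number of clinical centres, and it uses the total before inflation.
3. A total for three groups is inflated as if everyone came from a centre. It is then handed to two groups, and the third is added afterwards.

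At stake is whether the reader can rely on the stated basis for N, namely power of 0.8 after clustering and 10% dropout. The comparison of residential patients with outpatients matters most here. Objective 1 names it first, it depends wholly on recruitment, and the source study (patients against the general population) does not inform it.

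**Working it through.** **Inputs.** From Study 1, Data analyses: f = 0.15, three groups, two covariates, power 0.8, 25 centres, ICC 0.02, dropout 10%, 300 per patient group and 300 from ISTAT. Alpha is not stated; 0.05 is assumed.

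**1. Steps that reproduce.**
- Source effect size: f = (5.17 − 0.76)/(2 × 5) = 0.441, stated as 0.44.
- Base N from the noncentral F test: 432. The stated 435 (145 per group) has power 0.804.
- Design effect: 1 + (17.4 − 1) × 0.02 = 1.328, printed as 1.3.
- 435 × 1.3 = 566 and 435 × 1.328 = 578. The stated figure of about 570 lies between them.

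**2. Dropout: does not reproduce.**
- 600/570 = 1.053, and 1 − 570/600 = 5.0%.
- 600 × 0.9 = 540, below 570.
- 570/0.9 = 633.3, so 634 are needed. Even the weaker rule, 570 × 1.1, gives 627.
- Starting from the unrounded values does not help: 600 allows 5.75% loss on 565.5 and 3.7% on 577.7.

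**3. Cluster size.** DE = 1 + (m − 1) × 0.02:

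| Reading | m | DE |
|---|---|---|
| Plan: 435/25 | 17.4 | 1.33 |
| Patient share of 435: 290/25 | 11.6 | 1.21 |
| Planned recruitment: 600/25 | 24 | 1.46 |
| After 10% loss: 540/25 | 21.6 | 1.41 |
| If 35 centres join: 600/35 | 17.1 | 1.32 |

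With 25 centres, 17.4 is neither the planned size nor the patient share of 435. The average of 24 lies inside the stated range of 15 to 40.

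**4. Three groups against two.** On the plan's own basis, 570 over three groups is 190 per group, or 380 patients. With 10% dropout that is 380/0.9 = 423 (rounded up), against 600 planned.

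**5. Power of the design as planned.** Take 540 patients after 10% loss, 25 centres and DE 1.412 applied in full to the patients:
- Effective patients: 540/1.412 = 382, or 191 per group.
- Three-group test at f = 0.15 (noncentrality N × f²): power 0.90 for three groups of 191 (N = 573), and 0.95 with all 300 ISTAT subjects (N = 191 + 191 + 300 = 682).
- Residential against outpatient, two groups at f = 0.15 (d = 2f = 0.30): power 0.83. The smallest difference detectable with 80% power is d of about 0.29.

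**6. The source SD.** For a quantity confined to 0 to 24 h with mean μ, the SD cannot exceed √(μ(24 − μ)). At μ = 0.76 this is √(0.76 × 23.24) = 4.2 h, so an SD of 5 h is impossible for the general population. It enters the 0.44 but not the 435, which rests on 0.15.

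**The case against.** The strongest reply is that the errors do not leave the study too small. The plan calls 435 a total for three groups and adds the ISTAT group openly. Each patient group therefore has 300 against 190 required, even after the plan's own design effect. That surplus more than absorbs the thin dropout margin and the low design effect. This stands, and it settles the question of a shortfall.

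A reader might infer the opposite: that 600 should have been 654, or 727 with dropout, and that true power is 0.75 to 0.78. Those figures come from treating all 435 as clustered patients: 600/1.46 = 411 effective gives 0.78, and 540/1.412 = 382 gives 0.75. The text does not support that reading, because a third of the 435 belongs to a group that is not recruited in centres.

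The value of 1.46 also depends on the number of centres. The plan says about 25, but more than 35 sites had shown interest. With 35 the design effect is about 1.32, almost the printed figure. This stands as a limit on the size of the error. It does not rescue the calculation, which itself uses 25 centres and counts subjects who belong to none of them.

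Nor does the article require a multiplicity correction for the pairwise contrasts, so none is applied here. A condensed article may leave such detail to the full protocol or analysis plan.

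Finally, the SD is attributed to a cited study that is not at hand, so its origin cannot be checked, and it has no effect on N. What can be said is that the printed mean and SD cannot both hold.

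**Conclusion.** The written justification is wrong in three places, and no lack of power is shown. The dropout allowance is about 5%, not 10%; this needs no assumption beyond the plan's own 570 and 600. The design effect rests on a cluster size that does not describe the recruited patients: at 25 centres it is 1.46, or 1.41 after 10% loss, falling to about 1.32 if 35 centres take part. The stated power of 0.8 belongs to a design that is not being run, because a three-group total was assigned to two groups; this error is conservative.

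For the design as planned, power at f = 0.15 is about 0.90 to 0.95 for the three-group test and about 0.83 for residential against outpatient. These values assume alpha 0.05, 10% loss, 25 centres of equal size, ICC 0.02 and the full design effect on both patient groups. The impossible general-population SD is a separate slip without effect on N.

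This is a correction to make in the text. It changes neither the recruitment target nor the analysis.

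**What to change.** Keep 600 and rewrite the paragraph:

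- State 540 evaluable patients at 10% dropout, or state that the step from 570 to 600 allows for 5%.
- Apply the design effect to the two patient groups only, at the planned number of patients per centre, and give the number of centres assumed.
- Count the 300 ISTAT subjects separately, without a centre design effect.
- State alpha and the resulting power. If alpha is 0.05: about 0.90 to 0.95 for the three-group test at f = 0.15, and about 0.83 for residential against outpatient, with a smallest detectable d of about 0.29.
- Check the general-population SD of 5 h against its source and correct it.

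The cost is one rewritten paragraph and, if the 5% allowance is stated, a smaller dropout margin on paper. No extra patients are needed.
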